# Individualized Chinese medicine for the treatment of diabetic patients with dry eye disease

**DOI:** 10.1097/MD.0000000000018459

**Published:** 2020-01-03

**Keywords:** diabetes mellitus, dry eye disease, individualized treatment, single-case randomized controlled study, traditional Chinese Medicine

## Abstract

**Background::**

The high incidence of Diabetes mellitus (DM) has become a serious challenge for the global epidemic. Increased blood glucose leads to abnormal ocular surface structure and metabolic disorder in patients. DM is a high-risk factor for dry eye disease (DED), with high incidence and increased difficulty in treatment. The disease can cause discomfort, visual impairment, tear film instability and ocular surface damage, and even cause corneal erosion in severe cases, which has a serious impact on people's daily life. Traditional Chinese Medicine (TCM) plays an important role in the evaluation and treatment of DM and its complications. However, whether TCM treatment could improve the treatment efficacy of DM suffering from DED remains poorly understood.

**Objective::**

To investigate the curative effect of TCM for the alleviation of clinical symptoms in Diabetic patients with DED, and to evaluate its long-term efficacy.

**Methods::**

This trial is a single-case randomized, single-blind, placebo-controlled study. A total of 12 subjects will be recruited in this trial. The trial is divided into three cycles, and one cycle has 2 treatment periods. There is a washout period at each adjacent treatment stage. TCM individualized treatment and placebo will be randomized during the treatment period. The test period will last for 29 weeks, with 4 weeks for each treatment period and 1 week for each washout period to minimize carryover effects. Subjects will be selected by the researcher strictly in accordance with the inclusion and exclusion criteria. The outcomes will evaluate the efficacy of treatment by changes in the various observation indicators.

**Discussion::**

This study will realize a patient-centered outcome approach necessary to provide clinical researchers with the evidence that TCM treatment can effectively improve the objective indicators of the eye and systemic symptoms in Diabetic patients with DED.

**Trial registration::**

This study has been registered at the Chinese Clinical Trial Registry (http://www.chictr.org.cn, No. ChiCTR1900024481), (October, 2019).

## Introduction

1

Diabetes mellitus (DM) has emerged as one of the most major global public health problems,^[1]^ especially in developing nations such as China.^[2]^ It is reported that three in four people living with diabetes (352 million people) are of working age (i.e. between 20 and 64 years old), and this number is expected to increase to 417 million by 2030 and to 486 million by 2045.^[3]^ DM can cause a variety of systemic complications, most of which suffer from dryness of the eye, foreign body sensations, photophobia, and vision fluctuations. During the course of diabetes, microvascular damage to the lacrimal gland due to hyperglycemia, reduced lacrimal innervation as a result of autonomic neuropathy, reduced trophic support to lacrimal tissue, and reduced reflex tearing due to impairment of corneal sensitivity all contribute to the altered tear film status in diabetic patients.^[4]^ The International Dry Eye Workshop 2017 classified diabetes as a risk factor for aqueous-deficient dry eye disease (DED).^[4]^ The incidence of Diabetes combined with DED continues to rise due to changes in lifestyle and dietary preferences in recent years.

DED, also referred to as keratoconjunctivitis sicca, is a complex multifactorial disorder characterized by homeostatic disturbances of the ocular surface and tear film DED is one of the most common eye disorders, and the prevalence of adult populations in different parts of the world is estimated to be between 5% and 50%.^[5]^ There have been reported that the prevalence and severity of dry eye symptoms are higher in Asian ethnic groups than in the Caucasian population.^[6–7]^ The incidence of DED is correlated with the level of glycated hemoglobin: the higher the level of glycated hemoglobin, the higher the incidence of DED.^[8,9]^ Najafi et al. showed that the prevalence of DED in diabetic patients was 27.7%, and DED was significantly associated with glycosylated hemoglobin (HbA1c).^[10]^ Zou et al observed a prevalence of DED was 17.5% in a community-based type 2 diabetic patients, which was lower than that observed in hospital-based studies, but DM patients with poor metabolic control were more likely to develop DED.^[11]^ The course of Diabetes combined with DED is slow, and the inflammatory cascade is triggered by a long-term vicious circle of tear film instability and hyperosmolarity ensues, which may lead to progressive and irreversible changes in the ocular surface.^[12]^ Moreover, DED can have profound effects on the ocular comfort, vision, quality of life, work efficiency of patients, and increase the economic burden for both patients and society. At present, based on the treatment of primary disease, artificial tears are the first choice for the treatment of dry eye among patients with DM, but artificial tears can only relieve the symptoms of patients without treatment from the basic pathological mechanism.^[13]^ Therefore, there is an urgent need to develop novel therapeutic approaches for improving the overall condition of patients with diabetic dry eye.

Laboratory studies and clinical observations have showed that TCM plays an important role in the evaluation and treatment of diabetes and its complications,^[14–16]^ which can assist in delaying or preventing the progression of the disease. In recent years, research has been undertaken to explore the mechanism of action of TCM and its active ingredients, and how to use these active ingredients to develop new treatments for improved management of diabetes and its complications.^[17]^ Qiming Granule (QMG) has the function of Yiqi Shengjin, nourishing liver and kidney, Tongluo Mingmu and it can effectively treat diabetic complications by increasing retinal blood flow and improving the blood circulation to alleviate retinal hypoxia and ischemia.^[14]^ And it has been proved to be suitable for deficiency of qi-yin and blood stasis as the main TCM syndromes in microvascular complications in diabetes.^[14,18,19]^ However, it is unclear whether components in QMG are also effective against Diabetic patients with DED. Therefore, based on QMG, we designed to treat each patient with syndrome differentiation and to form individualized treatment to study its therapeutic effect on Diabetic patients with DED. In our study protocol, a single-case randomized controlled trial (N-of-1) will be used, which can highlight individualized diagnosis and treatment. TCM clinical treatment is based on the principle of “dialectical treatment”, and can determine the treatment plan according to each patient's own situation, which is in line with the features of N-of-1. Therefore, N-of-1 is very suitable for the clinical application of TCM study. Our study aims to evaluate the clinical efficacy of individualized treatment in Diabetic patients with DED and to explore individualized therapeutic assessment methods for TCM research.

## Methods

2

### Trial design

2.1

This is a single-case randomized controlled single-blind study. The study population comes from Ineye Hospital affiliated to Chengdu University of Traditional Chinese Medicine. Twelve subjects will be screened for diabetes with DED. The single participant who met the inclusion criteria of TCM clinical response underwent 3 cycles of treatment periods with 6 observation periods, 2 of which are in one cycle, including 4 weeks of TCM individualized treatment and 4 weeks of placebo. In each cycle of testing, each subject determines the order in which the two drugs are used simulant at random. All participants will continue their basic treatment during entire the trial period. There is no washout period at the beginning of the study and there is 1 week washout period at each adjacent treatment stage to make carryover effects minimized and observe the disease development.

The study will be conducted in October and November, 2019. The intervention will begin in November and December 2019 and it is planned to be concluded by September and October, 2019. The entire study experiment time is 29 weeks. Figure 1 shows the overall flow of the subject's drug treatment process. The protocol is compliant with the Standard Protocol Items: CONSORT extension for reporting N-of-1 trials (CENT) 2015.^[20]^ If the symptoms change and develop, patients will be offered the option of stopping a treatment period early and waiting for the other treatment period after a washout period or withdrawing the trial.

**Figure 1 F1:**
[figure not shown]
Flow Chart of Clinical Trial in Diabetes with dry eye disease. Note. The trial consisted of 3 cycles and is divided into six treatment periods. A/B treatment represents patients receiving TCM individualized treatment and placebo treatment are randomized. There are 4 weeks for each treatment period and a 1-week washout period at the end of treatment.

Due to the complex complexity of herbal ingredients, their onset time and half-life are not easily predicted from their pharmacokinetics or pharmacodynamics and a possible residual effect might be expected. Therefore, the treatment periods of each two adjacent pair will be separated by 1-week wash-out interval to minimize carryover effects.

### Classification of dry eye syndrome

2.2

DED can be divided into 2 types: aqueous tear-deficient (tear-deficient, lacrimal tear deficiency) and evaporative dry eye. Aqueous-deficient dry eye has two major subgroups: Sjögren and non-Sjögren syndrome. Evaporative dry eye may be intrinsic (e.g., due to meibomian gland dysfunction, low blink rate, or eyelid problems) or extrinsic (e.g., due to contact lens wear, preservatives in topical medications, or diseases of ocular surgeries).^[21]^ DM associated dry eye may be tear-deficient or evaporative dry eye.^[22]^

### Study population

2.3

#### Diagnostic criteria

2.3.1

The definition criteria of DED is based on the revised Japanese DED diagnostic criteria:

(1)the symptoms of dry eye diseases;(2)presence of either a quantitative or qualitative disturbance of the tear film (BUT ≤5 s or Schirmer I test ≤5 mm); and(3)presence of conjunctivo-corneal epithelial damage (fluorescein staining score ≥ 3 points, Rose Bengal staining score ≥ 3points, or lissamine green staining score ≥ 3 points).

A definitive diagnosis of DED was established only if all three criteria were present.^[23]^ New criteria for diagnosis and treatment of DM will be referred to the American Diabetes Association (ADA) criteria.^[24]^

The TCM syndrome differentiation type of deficiency of both qi-yin and blood stasis are based on the guidelines of TCM.^[25]^ The primary signs and symptoms include conscious dry eyes, a gritty or foreign body sensation, fatigue, burning sensation, eye irritation, tearing, photophobia, visual fluctuations, stinging or intermittent sharp pain (The first 3 items are required). The secondary signs and symptoms include

(a)qi-deficiency: shortness of breath, low voice or disinclination to talk, tired, lack of strength, spontaneous sweating;(b)yin-deficiency: thirst with liking for fluids, vexing heat in chest, palms and soles, dizziness and tinnitus, night sweats, constipation;(c)pale or dark tongue or petechia, little coating, thready and uneven pulse.

Among the above symptoms, Participants who suffer with the main primary signs and 3 to 4 species in each secondary symptom, combined with the tongue and pulse can be diagnosed with deficiency of both qi-yin and blood stasis.

#### Inclusion criteria

2.3.2

Patients who meet the following criteria will be considered for enrollment:

(a)patients with confirmed diabetes combined with DED;(b)comply with TCM syndrome differentiation standards;(c)between 18 and 75 years of age;(d)accepted the survey voluntarily and signed informed consent;(e)ability to return for study visits.

#### Exclusion criteria

2.3.3

Patients were excluded from participation in the study if any of the exclusion criteria were met:

(a)women who were pregnant or breastfeeding;(b)patients with any ocular surface disease, scarring, acute ocular infection, blepharitis, and an unwillingness to discontinue contact lens wear during the study;(c)receive any eye surgery within 3 months;(d)history of diseases that affect vital organs, including heart, liver, and kidney;(e)mental disorder;(f)participated in other clinical trials in recent 3 months.

#### Withdrawal criteria

2.3.4

Participants who meet any of the following conditions will be removed from the study:

(a)Patients with poor compliance who did not take drugs according to requirements of the study protocol were rejected;(b)voluntary withdrawal from the trial;(c)intolerant or allergic to the drug.

#### Participant recruitment

2.3.5

The trial will be set up and co-ordinated by academy of ophthalmology of Chengdu University of TCM. Subjects will be recruited from Ineye Hospital affiliated to Chengdu University of TCM, or they can be recruited online or by advertising.

### Intervention

2.4

All subjects in the trial will continue to receive basic medicine. After completing the TCM syndrome differentiation, the doctor gives the individualized treatment prescription and the control prescription (placebo). The individualized treatment will follow routine practice of Chinese herbal medicine (CHM). Both the drugs are Chinese medicine granules and uniformly processed and provided by the pharmacy of Ineye Hospital affiliated to Chengdu University of TCM. Written consent will be obtained from all participants prior to the start of the program.

Experimental group: QMG consists of 8 herbs, namely Astragalus membranaceus, Radix Rehmanniae, Fructus Lycii, Radix Puerariae, Cassia Seed, Cattail Pollen, Motherwort Fruit and Hirudo. The individualized TCM are as follows: blood deficiency, plus white peony, Angelica; yin deficiency and fire wang signs clearly, plus Anemarrhena asphodeloides, Cortex Phellodendri; qi deficiency, plus Radix ginseng, Schisandra; blood stasis, plus Panax notoginseng, Salvia Miltiorrhiza; yang deficiency, plus Eucommia, Herba Epimedii; turbid-phlegm, plus Rhizoma Pinelliae, Poria cocos; water-dampness, plus Grifola umbellata, Alisma; qi stagnation, plus Fructus aurantii, Dried tangerine peel. The therapeutic formula will be adjusted based on the patient's clinical performance each treatment cycle.

Placebo control group: The preparation method of traditional Chinese medicine placebo is made by using a low proportion of drugs and auxiliary materials, and 10% of the test drugs are used to increase the similarity. Lactose is mixed with flour as a diluent, edible caramel, sunset yellow and lemon yellow pigment are used as a coloring agent, and edible bittering agent and aspartame are used as a flavoring agent. Made by mixing, drying, pulverizing, sieving, granulating, and finishing. It is basically consistent with the test drugs in terms of appearance, smell, color, taste and packaging. Both groups of drugs are provided by Sichuan New Green Pharmaceutical Technology Development Co., Ltd. Method of administration: took mixed with warm boiled water, 3 times a day.

### Outcomes

2.5

Patients need to be at baseline, treatment week 4, week 5, week 9, week 10, week 14, week 15, week 19, week 20, week 24, week 25, and week 29 visits. Various eye examinations are performed on the right eye of each patient and each visit requires observation and recording of measurement indicators. An overview of specific measurements and time points of data collection are provided in Table 1.

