#### Eye examination

2.5.2

Schirmer I tests (without anesthesia): performed by placing a strip in the unanesthetized eye over the lower lid margin, midway between the middle and outer third and recording the length of the strip that was wetted after 5 minutes.

The noninvasive tear film break-up time (NITBUT): NITBUT measurements are evaluated using the Keratograph 5 M (OCULUS Optikgeräte GmbH, Wetzlar, Germany). The professional operator will note the first NITBUT (NITBUTf), and the average value of the intervals after blinking on the corneal viewing area are recorded as the average NITBUT (NITBUTav).

Meibomian gland loss: Images showing Meibomian gland loss of the right upper eyelid were obtained using the OCULUS Keratograph ocular surface analyzer in accordance with the manufacturer's instructions. Analyze and record the ratio of meibomian gland dropout area to the total area.

Fluorescein staining: Corneal-conjunctiva staining was accessed using the cobalt-blue filter of the slit-lamp light source through a Wratten 12 yellow filter, 2 minutes after instilling 5 mL of 2% sodium fluorescein. The eye is divided into three equal compartments: the cornea, the nasal conjunctiva and the temporal conjunctiva. The staining of each region is graded from 0 to 3 points. A score of 0 represented no staining; a score of 1 represented 1-30 staining dots; a score of 2 scores represented > 30 staining dots; a score of 3 scores represented total staining with ulcer and filaments. The final stain scores are the sum of the ranks of the three regions.

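### Eye signs are measured in the right eye only, but a patient can enter without the right eye meeting the dry eye definition

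*Protocol article*

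**What the plan says.** Section 2.5 (Outcomes) settles the measured eye in advance: "Various eye examinations are performed on the right eye of each patient". Section 2.5.2 (Eye examination) does the same for meibography: "Images showing Meibomian gland loss of the right upper eyelid were obtained". No left-eye outcome is described.

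The disease requirement in 2.3.2 (Inclusion criteria) is at patient level: "patients with confirmed diabetes combined with DED". The definition behind it, in 2.3.1 (Diagnostic criteria), has three parts:

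- symptoms;
- "presence of either a quantitative or qualitative disturbance of the tear film (BUT ≤5 s or Schirmer I test ≤5 mm";
- "presence of conjunctivo-corneal epithelial damage (fluorescein staining score ≥ 3 points", with two other stains at the same threshold as alternatives.

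The combining rule is "A definitive diagnosis of DED was established only if all three criteria were present". None of these lines names an eye or says that the parts must be met in one and the same eye. The exclusion criteria in 2.3.3 add nothing on this.

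**The concern.** Entry thresholds for tear film and staining normally do two jobs. They establish that the patient has the disease, and they make sure that the measured eye starts with something to improve. Here only the first is secured, because the thresholds need not be met by the eye that is then followed for 29 weeks.

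Two uses of the data are exposed. The first is the pooled effect on the eye signs (2.11). The abstract's discussion and section 3 both rest the trial's claim partly on objective eye measures. The second is the per-patient judgement of effectiveness announced in 2.6. A right eye that was never clearly diseased may show no difference between TCM and placebo for that reason alone. Section 3 already concedes that the self-controlled design can produce false negatives, and this would be an avoidable source of them. An analysis plan could not repair it later, since no left-eye outcomes are described.

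**Working it through.** **Step 1. The two rules side by side.**

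| | Entry (2.3.1, 2.3.2) | Outcome (2.5, 2.5.2) |
|---|---|---|
| Unit | patient | right eye |
| Tear film | BUT ≤5 s or Schirmer I ≤5 mm, eye not named | Schirmer I and NITBUT (first and average), right eye |
| Staining | score ≥3 on any of three stains, eye not named | fluorescein sum of three regions, each 0–3, right eye |
| Gland loss | not a criterion | right upper eyelid |
| Symptoms | patient level | OSDI and TCM syndrome score, patient level |

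**Step 2. Who can enter under the text.** Two kinds of patient satisfy all three criteria without a qualifying right eye: one whose left eye alone meets criteria (2) and (3), and one who meets criterion (2) in one eye and criterion (3) in the other.

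**Step 3. What that does to room for change.** The fluorescein score runs from 0 to 3 × 3 = 9. A right eye that starts at 0 cannot fall. On the other signs, failing the definition only reduces the likely room. An eye with BUT 3 s, Schirmer 4 mm and staining 2 fails criterion (3), yet can still improve on all three measures. Failing the definition says nothing about gland loss, which is not part of it.

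**Step 4. Size.** The document gives no rate of one-sided or asymmetric disease, so the number of affected patients, k, is assumed. Take the worst case, in which a non-qualifying right eye shows no treatment effect at all. The mean over 12 patients then keeps the share (12 − k)/12:

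- k = 1: 11/12 = 0.917
- k = 2: 10/12 = 0.833
- k = 3: 9/12 = 0.750

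For a given k this is the largest dilution, because by step 3 such eyes may still respond in part.

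**Step 5. Chance that it happens at all.** Let f be the assumed share of enrolled patients whose right eye does not qualify. Then P(at least one of 12) = 1 − (1 − f)^12:

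- f = 5%: 0.46, expected 0.6 patients
- f = 10%: 0.72, expected 1.2 patients
- f = 20%: 0.93, expected 2.4 patients
- f = 30%: 0.99, expected 3.6 patients

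Even a small share makes one affected patient plausible, and one patient is 1/12 = 8% of the series.

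There is no figure in the plan to reproduce. Section 2.6 states that the number of participants was not chosen for testing group effects, so the dilution is not converted into a loss of power.

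**The case against.** The strongest reply is that this is silence in a condensed article, not an error. Baseline is one of the visits listed in 2.5, so the entry tests may be the right-eye tests made at that visit, and the full protocol may say so. This is fair as far as it goes: 2.3.1 and 2.5 do not contradict each other, and screening may well use the right eye in practice. It does not dispose of the point. The article states both rules in detail, thresholds on one side and the eye on the other. Followed as written, they admit eyes that do not qualify.

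A second reply is that diabetic dry eye has systemic causes, as the Introduction describes, so most patients will be affected in both eyes. Also, if left-only and right-only disease are equally common, 3 of 12 left-only patients would imply about 3 right-only patients, so half the series would be one-sided. This stands as a reason to regard the upper end of the range as unlikely if left-only disease is the main route. It does not show that the number is zero.

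A reader might infer that affected patients cannot improve on any eye sign and that their individual trials are worthless. The document does not support this. Only staining at its floor is truly unable to improve. OSDI and the TCM syndrome score are not tied to an eye, and relief of symptoms is part of the stated objective. Nor is either treatment favoured: each patient receives both treatments and the same right eye is compared under each, so the only direction of error is towards no difference.

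**Conclusion.** The point holds in a limited form. The plan measures the right eye but does not require the right eye to qualify. The consequences are a diluted effect on the eye signs and, for an affected patient, a possible false finding of no effect on those signs. The patient-level scores are untouched.

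The size is unknown and may be small. The retained effect of 92% to 75% rests on two assumptions: that 1 to 3 of the 12 right eyes do not qualify, which the document neither supports nor excludes, and that such eyes show no effect at all, which is the extreme case. It is worth correcting because the remedy is one sentence and the loss cannot be recovered once the trial has run.

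**What to change.** Add to 2.3.2 that the right eye itself must meet diagnostic criteria (2) and (3) of 2.3.1 at baseline. Section 2.5 then stays as it is, and both criteria are tied to the eye that is followed.

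**Cost.** One sentence, and a few candidates with a non-qualifying right eye screened out.

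**What it does not do.** It does not secure room to improve on every eye sign. Criterion (2) can be met by BUT or by Schirmer alone. Criterion (3) can be met by a stain other than fluorescein, which is the only stain followed as an outcome. Gland loss is not a criterion.

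**Alternative.** The study eye could be defined as the qualifying eye, or the worse one if both qualify, and kept for all visits. This loses no candidates, but 2.5 and the meibography text in 2.5.2 would have to change. Picking the worse eye on its baseline value also brings regression to the mean into any comparison with baseline, which 2.6 envisages. The right-eye entry rule is the simpler choice.
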